## Abstract

**Background:**

Osteoporosis affects over 220 million people worldwide, and currently there is no ‘cure’ for the disease. Thus, there is a need to develop evidence-based, safe and acceptable prevention strategies at the population level that target multiple risk factors for fragility fractures to reduce the health and economic burden of the condition.

**Methods/design:**

The *Osteo-cise: Strong Bones for Life* study will investigate the effectiveness and feasibility of a multi-component targeted exercise, osteoporosis education/awareness and behavioural change program for improving bone health and muscle function and reducing falls risk in community-dwelling older adults at an increased risk of fracture. Men and women aged ≥60 years will participate in an 18-month randomised controlled trial comprising a 12-month structured and supervised community-based program and a 6-month ‘research to practise’ translational phase. Participants will be randomly assigned to either the *Osteo-cise* intervention or a self-management control group. The intervention will comprise a multi-modal exercise program incorporating high velocity progressive resistance training, moderate impact weight-bearing exercise and high challenging balance exercises performed three times weekly at local community-based fitness centres. A behavioural change program will be used to enhance exercise adoption and adherence to the program. Community-based osteoporosis education seminars will be conducted to improve participant knowledge and understanding of the risk factors and preventative measures for osteoporosis, falls and fractures. The primary outcomes measures, to be collected at baseline, 6, 12, and 18 months, will include DXA-derived hip and spine bone mineral density measurements and functional muscle power (timed stair-climb test). Secondary outcomes measures include: MRI-assessed distal femur and proximal tibia trabecular bone micro-architecture, lower limb and back maximal muscle strength, balance and function (four square step test, functional reach test, timed up-and-go test and 30-second sit-to-stand), falls incidence and health-related quality of life. Cost-effectiveness will also be assessed.

**Discussion:**

The findings from the *Osteo-cise: Strong Bones for Life* study will provide new information on the efficacy of a targeted multi-modal community-based exercise program incorporating high velocity resistance training, together with an osteoporosis education and behavioural change program for improving multiple risk factors for falls and fracture in older adults at risk of fragility fracture.

**Trial registration:**

Australian New Zealand Clinical Trials Registry reference ACTRN12609000100291

## Background

Osteoporosis and related fractures are a serious public health problem worldwide because of the associated morbidity, mortality and health care costs. In 2011, 1.2 million Australians were diagnosed with osteoporosis and another 5.4 million had osteopenia and are therefore at risk of fragility fracture [1]. Due to the demographic trend towards an ageing population, the incidence of osteoporosis-related conditions is projected to rise to three million people by 2021, with a fracture occurring every three and a half minutes unless effective prevention strategies are implemented [2]. For those that sustain a hip fracture, it is estimated that more than 20% will die within 6 to 12 months post fracture [3], almost 50% will require long-term nursing care [2] and up to 80% of those who survive will fail to regain their pre-fracture level of function [4].

Currently the medical paradigm of a ‘cure’ for osteoporosis is less than ideal because the pharmacological agents available are directed to those who have already had fragility fractures or have a high absolute fracture risk and the lowest bone density. However, in women it is estimated that more than 50% of fragility fractures occur in those with ‘osteopenia’ (BMD T-score −1.0 to −2.5 SD) and not ‘osteoporosis’ (T-score ≤ −2.5 SD) [5]. Furthermore, since most osteoporotic fractures are due to a fall or minimal trauma [6,7] there is considerable interest in identifying safe, effective and widely accessible community-based strategies for addressing multiple fracture-related risk factors, particularly reduced bone density, muscle wasting and weakness, poor balance and impaired gait and mobility which increase the risk of falling.

Current national and international consensus osteoporosis management guidelines recommend a combination of weight-bearing and resistance training with challenging balance exercises to improve multiple risk factors for falls and fracture [8]. At present however, there is no scientific consensus regarding the optimal mode and dose (type, frequency, duration and intensity) of exercise that can simultaneously enhance bone and muscle health and improve functional ability in older adults at risk of osteoporosis, falls and fractures. A meta-analysis of randomised controlled trials in older adults reported that multi-component exercise programs incorporating a combination of weight-bearing impact exercise (jogging, stair-climbing, jumping activities) and progressive resistance training (PRT) were most effective for maintaining bone mineral density (BMD) or preventing bone loss at clinically relevant sites such as the hip and spine [9].

Programs incorporating high intensity PRT alone are also particularly effective for improving muscle strength, mass and size [10] and may attenuate bone loss if they incorporate targeted hip and spine loading exercises [11,12]. However, the effectiveness of traditional PRT on other fall-related risk factors such as balance, gait, mobility and postural sway, are mixed [13-15]. This has been attributed in part to the fact that most PRT programs encourage slow velocity contractions (2 to 4 seconds concentric phase) at a moderate to high percentage of maximal force. However, many common tasks related to mobility and daily perturbations require rapid co-ordinated contractions within 50–200 msec, which is less than the time needed to achieve maximal muscle force (400–600 msec) [16]. Therefore, programs which focus on improving the ability to generate force quickly, which is often referred to as power training, and that are specific to tasks of daily living, are likely to be more relevant to improving muscle function and reducing the risk of falls.

The clinical relevance of maintaining lower extremity muscle power has been demonstrated in studies which have shown that relative to muscle strength, deficits in muscle power are a stronger predictor of disability and falls in older people [17,18]. Power training, which is also referred to as high velocity (HV) PRT, is characterised by rapid concentric (lifting or pushing) movements followed by a slower eccentric (lowering) phase. Several recent reviews and meta-analyses of the limited randomised controlled trials available have demonstrated that high velocity PRT is safe and feasible for older adults and may be a more effective training method for improving functional outcomes (e.g. chair rising time, stair climbing, walking speed) compared to traditional PRT, despite producing similar gains in muscle strength [19]. Moreover, there is also evidence from one previous intervention indicating that high velocity PRT is more effective for slowing the rate of bone loss than traditional PRT [20]. Based on these findings, we hypothesize that high velocity PRT may be the optimal training method for improving both bone health and muscle function. Whether the inclusion of high velocity PRT into an exercise program can reduce falls in the elderly has not been examined.

For older people, preventing falls is imperative as around 90% of all osteoporotic fractures, particularly hip fractures, occur as a result of a fall [21,22]. Fall-related injuries are also associated with considerable morbidity, mortality and healthcare utilization. It has been reported that approximately 30% of people who fall experience a serious injury, and 5 to 10% suffer a fracture with up to 1.5% suffering a hip fracture [23,24]. Falls are also associated with increased disability, loss of independence and reduced physical activity, which lead to reduced quality of life [25]. Regular exercise is known to be one of the most important strategies for reducing falls risk, but not all forms of exercise are equally effective. In a recent systematic review and meta-analysis of 54 randomised controlled trials (RCTs), exercise was found to reduce the risk of falls by 16% in older people [26]. In this study, it was reported that the most effective mode of exercise for preventing falls was high-challenge balance training and the inclusion of walking in any exercise program tended to attenuate the beneficial effects [26]. The authors’ earlier meta-analysis of RCTs reported that traditional moderate or high intensity PRT alone did not significantly reduce falls risk [15]. A more recent Cochrane review reported that multi-component group exercise, typically including resistance and balance training, reduced the rate of falls by 22% and falls risk by 17% in older adults aged 60 years and over [27]. In this review, exercise was the only intervention to reduce both fall rates and future falls risk; other interventions such as home modification strategies, vitamin D supplementation, medical review and cataract surgery only reduced one of these outcomes. While these findings support the concept that targeted exercise programs are likely to be most effective for optimising muscle function and reducing falls, from a public health perspective it is important to evaluate whether such programs can be successfully and safely translated from the research setting into the community.

One of the key challenges facing health-care professionals when implementing any community-based exercise programs is how to enhance adoption and adherence to the program and achieve sustained behaviour change. In older adults, there is considerable evidence that the use of behavioural theory-based strategies can effectively enhance the adoption to and maintenance of exercise programs [28,29]. Specifically, the Transtheoretical (Stages of Change) Model which matches an intervention to an individuals’ level of motivational readiness, and the Social Cognitive Theory (SCT) that includes both social and cognitive elements which can influence behaviour (e.g. self-efficacy, social support, self monitoring), appear to be particularly effective behavioural management strategies to maximise adoption, increase motivation and adherence, and minimise attrition from exercise programs [28,30,31]. There is also evidence that interventions which incorporate patient education can improve knowledge, sustainability in behaviour change and adherence to osteoporosis prevention guidelines [32,33]. Therefore, we believe that the design of any community-based osteoporosis, falls and fracture prevention program should include a targeted exercise program with soundly based behavioural strategies and patient education to achieve the greatest sustained benefits.

This paper describes the methods of the *Osteo-cise: Strong Bones for Life* trial; an 18-month community-based randomised controlled trial designed to evaluate the effectiveness and feasibility of an evidence-based, multi-modal exercise, osteoporosis education and behavioural change program for improving bone health, muscle power and function in community-dwelling older adults at increased risk for falls and fracture. Secondary aims of the study are to assess the effects of the intervention on: 1) trabecular bone microarchitecture; 2) lower limb and back muscle strength; 3) falls incidence, and 4) health-related quality of life. We will also conduct a cost-utility analysis to facilitate the cost effectiveness compared with other interventions targeted across a range of chronic disorders. The long-term goal is that the *Osteo-cise: Strong Bones for Life* program will serve as a model for future osteoporosis and falls prevention programs that can be implemented within the community with the aim of reducing fracture incidence and related risk factors for fracture, and consequently reduce osteoporosis-related health care costs and morbidity.

## Methods/design

### Study design

*Osteo-cise: Strong Bones for Life* is an 18-month multi-faceted randomised controlled trial involving community-dwelling men and women aged 60 years and over at increased risk of falls and fractures. The trial is divided into two phases: 1) a 12-month community-based structured and supervised intervention incorporating a multi-modal exercise program in conjunction with an osteoporosis education/awareness and a behavioural change program, and 2) a 6-month ‘*research to practise’* translational period in which each community-based health and fitness centre will aim to continue to implement the *Osteo-cise: Strong Bones for Life* program independently of research staff. This translational phase is designed to evaluate the sustainability of the program in the ‘real world’. The trial is managed by the Department of Medicine, Northwest Academic Centre, The University of Melbourne, Western Hospital, Australia and has been approved by the Melbourne Health Human Research Ethics Committee (HREC 2008.136). The study is also registered with the Australian New Zealand Clinical Trials Registry [Reference ACTRN12609000100291].

### Participants

Men and women aged 60 years and over living independently in the community in the Western suburbs and surrounding regions of Melbourne, Australia, who fulfil the defined inclusion criteria outlined below will be invited to participate in the study.

#### Inclusion/exclusion criteria

Eligibility to participate in the study will be based on a three step screening process. First, all participants who enquire about participating in the study will be initially screened via the telephone. Participants must meet the following criteria: i) aged ≥60 years; ii) BMI <40 kg/m^2^; iii) no history of osteoporosis; iv) not undertaken resistance training and/or weight-bearing impact exercise more than once a week in the past three months; v) be willing to be randomised into either the ‘*Osteo-cise’* intervention or usual care control group, and vi) be willing and able to travel to a local health and fitness centre three times per week for 18 months to complete the exercise program. Participants will be excluded from the study on the following criteria: i) current smoking; ii) current or prior (past 6 months) use of hormone replacement therapy (>0.625 mg/d premarin or equivalent estrogen); iii) having sustained a low trauma fragility fracture in the past 6 months; iv) any medical condition (e.g. type 1 diabetes, chronic kidney failure or liver disease, cancer) or use of medication known to influence bone metabolism or fracture risk (e.g. glucocorticoids, thiazide diuretics, anticonvulsants, bisphosphonates); v) initiating calcium or vitamin D supplementation in the preceding 6 months, or vi) expected travel of greater than 6 weeks in the next 18 months.

Potential participants will then have a DXA bone mineral density (BMD) scan and be eligible for randomisation if they are osteopenic (T-score between −1.0 and −2.5 SD) at the total hip, femoral neck or lumbar spine. Those with osteoporosis (T-score ≤ −2.5 SD) will be excluded and advised to consult their physician for follow-up care. Participants with normal BMD (greater than −1.0 SD) will complete a short falls and fracture risk questionnaire, adapted from Sanders et al. [34] (Table 1). Those with a total risk score of three points of higher will also be eligible to participate in the study. All eligible participants will be required to obtain approval from their local doctor to clear them of any contraindicated medical conditions to exercise, based on American College of Sports Medicine (ACSM) guidelines [8]. Written consent will also be obtained from all participants prior to commencing the program.

**Table 1 T1:** **Falls and fracture risk questionnaire for inclusion into the ****
*Osteo-cise: Strong Bones for Life *
****study**

**Risk Factor**	**Guidelines**	**Value**	**Score**
History of Falling ^1^	Self-reported risk of falling (2 or more falls past year)	3	
Low trauma fracture ^2^	Since age of 50 years	3	
Parental hip fracture	Did either of your parents suffer a hip fracture?	3	
Age	>75 years	2	
Menopause status	Early menopause or hysterectomy (<45 yr)	2	
Inability to rise from a chair without using arms	Are you able to rise from a chair without using your arms?	2	
Medication use	Are you currently taking four or more medications?	2	
Below average BMD	Proximal femur bone density T-score between 0.0 to –1.0 SD	2	
Thinness	BMI <20	2	
High risk of low vitamin “D” or calcium	“Do you spend less than 10 minutes per day outdoors (with part of your body exposed to sunlight), without taking vitamin D supplements”		
	OR	1	
	“Do you avoid, or are you allergic to milk or dairy products, without taking calcium supplements”		
**Score ≥ 3 = Eligible for the study**		**Total**	

^1^ A fall is defined as an event which results in a person coming to rest inadvertently on the ground or floor or other lower level.

^2^ A low trauma fracture is defined as any fragility fracture (e.g. hip, spine, forearm, humerus, pelvis, ribs) from a standing height or less.

#### Recruitment of participants

Participants will be recruited into one of two cohorts approximately 3 months apart in order to assist with the timely implementation and management of the intervention. A number of different strategies will be used to attract potential participants based on our experience from conducting previous trials in older adults [35,36]. This will include developing advertisements (paid), media releases and general interest articles for a range of media including local radio, television, state and local newspapers and council/community newsletters. Flyers will also be distributed to health professionals and community groups within the local area and posters displayed on notice boards at Rotary and Probus clubs, lawn bowling clubs, senior citizens groups, hospitals, medical centres, supermarkets and pharmacies. Information sessions will be delivered to local community seniors groups. Finally, participants already enrolled in the study will also be asked to recommend the study to family and friends.

#### Randomisation

Following baseline testing participants will be randomised into either the *Osteo-cise: Strong Bones for Life* program or a self-management control group, stratified by sex, by an independent staff member not involved in the study using a computer generated random numbers table (Microsoft Excel). To avoid any potential contamination any couples enrolled in the study will be randomised into the same group. A flow diagram of the study protocol is outlined in Figure 1.

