##### *1. ‘*Osteo*-cise’: Targeted Osteoporosis Exercise Program*

Participants randomised to the Osteo*-cise* group will be instructed to train at their nearest *Osteo-cise* health and fitness centre on three non-consecutive days per week for 18 months. The gymnasium membership for all participants during the initial 12 months will be subsidised. Exercise sessions will be conducted in small groups (a maximum of 10 per group) and monitored by qualified and certified exercise trainers who have completed the Osteo-*Instruct* training workshop. Before commencing the program, all participants will be required to attend an orientation session at their selected leisure facility to become familiar with the aims and design of the training program and the rules and regulations of each health and fitness centre.

The initial 12 months of the *Osteo-cise* program will be divided into a 4-week ‘Adoption Phase’ followed by four distinct 12-weekly mesocycles (Table 2). Each mesocycle is further divided into three 4-weekly microcyles which are designed to promote a sense of achievement and become progressively more challenging. Every session of the 4-week ‘Adoption Phase’ and the first week of each mesocycle will be supervised by *Osteo-cise* trainers. For the remaining 11 weeks of each mesocycle, participants will attend one scheduled supervised session per week with their designated trainer and two additional sessions independently or with fellow participants. All participants will be instructed to consult other on-site gym staff if they require assistance with their exercise program. Each session is intended to take approximately 60 minutes to complete and will comprise of a warm-up, high velocity progressive resistance training (HV-PRT) using machine and free weights, moderate impact weight-bearing exercises, high challenge balance and mobility exercises, core muscle stabilization exercises and flexibility (stretching) exercises. All programs will be individually tailored and designed to follow the key training principles of specificity and progressive overload. To assist trainers with exercise selection for each participant and to ensure correct technique and exercise progression, trainers will be provided with an *Osteo-cise* exercise manual which will include detailed explanations and illustrations for all key exercises.

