### Self-management control group

The self-management control group will serve as the comparison group in the intervention. Participants assigned to this group will receive general consumer information taken from Osteoporosis Australia fact sheets, including: “What is osteoporosis?”, “What are the risk factors for osteoporosis?” and “Calcium, vitamin D and exercise tips for preventing osteoporosis”. The aim is to enable these participants to actively take charge of their own musculoskeletal health and make educated decisions to seek further medical information and appropriate services to help prevent osteoporosis, falls and fractures. This group will undertake exactly the same testing protocol as the intervention group, but will not participate in the structured *Osteo-cise* program.

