### Statistical analyses

Statistical analyses will be computed using STATA statistical software (version 11.0, Stata Corp, College Station, TX). Baseline and demographic data will be presented using descriptive statistics. All intervention data will be analysed according to the principle of intention-to-treat (ITT) and adjusted for multiple comparisons where appropriate. Non- normally distributed data will be transformed prior to analysis. Comparisons between the groups for all continuous primary and secondary outcomes variables will be made using repeated measures analysis of variance (ANOVA) for both time and group-by-time interactions. ANOVA or analysis of covariance (ANCOVA) will be used for absolute and/or percent changes after 12 and 18 months after adjusting for relevant confounders. Falls will be analysed according to the rate of falls per person-year, the proportion sustaining one or more falls and injurious falls during follow-up. The number of falls will be analysed using Poisson regression models with robust standard errors to allow for non-independence of multiple events for the same participant and negative binomial regression models allowing for overdispersion.

Cost utility analysis: Cost data is often skewed and thus not normally distributed. Therefore the Kruskal-Wallis one-way analysis of variance will be used to test the difference in cost and quality of life between the ‘usual care’ and exercise groups. To investigate the difference in cost between the groups, the transformed cost variable will be used as the dependent variable in a multivariable ordinary least square (OLS) regression model. All data will be presented as means ± SD or 95% CI unless stated. The significance level will be *p* < 0.05 or smaller where adjusted for multiple comparisons.

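### Couples are allocated as a unit, but the stated models carry no couple term; if partners' changes are positively correlated, standard errors are understated, probably slightly

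*Protocol article*

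**What the plan says.** Under Randomisation, allocation follows baseline testing and is "stratified by sex, by an independent staff member not involved in the study". To limit contamination, "any couples enrolled in the study will be randomised into the same group". The section does not say how a couple is drawn from the sex-stratified list, or whether both partners must have completed baseline before either is allocated. Under Recruitment of participants, there are two cohorts about three months apart, and "participants already enrolled in the study will also be asked to recommend the study to family and friends".

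Under Statistical analyses, "Comparisons between the groups for all continuous primary and secondary outcomes variables will be made using repeated measures analysis of variance (ANOVA"), testing time and group-by-time terms. In addition, "ANOVA or analysis of covariance (ANCOVA) will be used for absolute and/or percent changes after 12 and 18 months after adjusting for relevant confounders". Neither model is given a couple, household, training-group or centre term. Dependence between observations is mentioned once, for falls: the Poisson model has robust errors for several events in the same person.

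Delivery differs by arm. In the exercise program section, "Exercise sessions will be conducted in small groups (a maximum of 10 per group"). Outside the 4-week adoption phase and the first week of each mesocycle, "participants will attend one scheduled supervised session per week with their designated trainer and two additional sessions independently or with fellow participants". Controls "will not participate in the structured" program, so they are not grouped.

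**The concern.** When two people always receive the same allocation, they do not contribute two independent allocations. Repeated measures ANOVA handles correlation between visits of one participant, but it takes different participants as independent, and so do ANOVA and ANCOVA on change scores. Spouses may resemble each other in their response. In the intervention arm they may also train at the same centre. If so, the variance of the between-arm difference exceeds what the models report, p-values for BMD and stair-climb power are too small, and confidence intervals are too narrow.

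Two related matters follow from the same rule. First, a male-female couple spans both sex strata, so both partners' assignments cannot come independently from their own lists. Second, if a partner enrols after the first has been allocated, the second allocation can be known before that person joins. Separately, shared training groups in one arm may add correlation there.

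**Working it through.** **Plan's own sample size figure.** The inputs in the Sample size section are a difference of 1.8, an SD of 3.5, two-sided 0.05 and 60 per group.

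- Needed for 90% power: 2 × (1.960 + 1.282)² × (3.5/1.8)² = 79.5, so 80 per group.
- Power at 60 per group: 1.8 / (3.5 × √(2/60)) = 2.817, and Φ(2.817 − 1.960) = 80.4%.

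The stated 90% does not reproduce. This is a separate error, but it sets the baseline: any loss from clustering starts from about 80%. No design effect is included in the calculation.

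**Couples (both arms).** Let f be the share of participants in couples and ρ the within-couple correlation of the change. Among n participants in an arm there are fn/2 pairs, so the variance of the arm total is nσ² + 2 × (fn/2) × ρσ² = nσ²(1 + fρ). The true standard error is √(1 + fρ) times the one reported. The true type I error of a nominal 5% test is 2 × [1 − Φ(1.96/√(1 + fρ))]. The article gives neither f nor ρ, so all values below are assumed.

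| f | ρ | Variance factor | SE ratio | Type I error | Power at 60 per group |
|---|---|---|---|---|---|
| 0.10 | 0.05 | 1.005 | 1.0025 | 5.06% | 80.2% |
| 0.20 | 0.10 | 1.020 | 1.010 | 5.23% | 79.6% |
| 0.20 | 0.30 | 1.060 | 1.030 | 5.70% | 78.1% |
| 0.30 | 0.30 | 1.090 | 1.044 | 6.05% | 77.0% |

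**Training groups (intervention arm only).** With groups of size m, the arm's variance factor is 1 + (m − 1) × ICC. The SE ratio for the difference is the square root of the mean of that factor and 1. With m = 10, the stated maximum:

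- ICC 0.01: factor 1.09, SE ratio √1.045 = 1.022, type I error 5.5%, power 78.7%.
- ICC 0.05: factor 1.45, SE ratio √1.225 = 1.107, type I error 7.7%, power 72.1%.

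**Both together** (f = 0.20, ρ = 0.10, m = 10). The arm factors are 1.11 and 1.02 at group ICC 0.01, and 1.47 and 1.02 at 0.05. The SE ratios are 1.032 and 1.116, type I errors 5.8% and 7.9%, and power 77.9% and 71.4%, against 80.4% with no clustering.

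**The case against.** The strongest reply has four parts.

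1. **This is a condensed article.** A cluster term could sit in an analysis plan that is not shown. That would excuse silence, but the article is not silent: it names the models for all continuous outcomes, names the one form of dependence it allows for, and sets a rule that creates another.

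2. **The couple effect is small, and large correlations are hard to support.** This stands. The BMD section gives a femoral neck CV of 1.5%. If that applies at each visit, measurement error alone contributes 2 × 1.5² / 3.5² = 37% of the assumed variance of change, and partners cannot share that part. A type I error of 6.9% requires 40% of participants in couples and an ICC of 0.4, and nothing in the article supports either value. Both arms also receive the same calcium and vitamin D.

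3. **Training groups form after individual randomisation.** If the program affected nobody, later grouping would not invalidate the comparison. Also, 10 is a maximum, programs are individually tailored, and for most of the year only one of three weekly sessions is supervised. This stands, and it is why the group term is a sensitivity analysis.

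4. **The concealment problem is hypothetical.** Randomisation follows baseline testing and is done by independent staff, and no text describes a late partner inheriting an allocation. A reader might infer that concealment is broken. The documents show only that no rule prevents it.

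A reader might also infer that the standard errors are certainly too small, or that power near 70% is the price of clustering. The first requires a positive correlation that the article does not document. The second overlooks that the plan's own inputs give about 80% before any clustering.

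**Conclusion.** The randomisation rule and the stated analysis do not match: couples are one unit at allocation and two independent people in the models. That mismatch holds whatever the correlation, which only sets the size of the consequence. Under the assumed 10-30% of participants in couples and ICC 0.05-0.30, standard errors are understated by about 0.25% to 4.4%. This is enough to move a borderline result, but not to change a clear one. Training groups could matter more, with a standard error about 2% to 11% larger at groups of 10 and ICC 0.01-0.05. That rests on assumed values, affects one arm only, and is not a defect of the randomisation. The sex-stratum and late-partner points are gaps in the allocation procedure, the second arising only if a partner enrols late.

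**What to change.** - **Primary analysis.** Record a household identifier, with single participants as households of one. Use household-clustered robust standard errors, or a couple random intercept, for the BMD, stair-climb and falls models. For falls, clustering on household instead of participant also covers repeated events in one person.
- **Sensitivity analysis.** Record the training group and fit a partially nested model with a group effect in the intervention arm only.
- **Allocation.** Randomise each couple once, as one unit in its own stratum, after both partners have completed baseline testing. This removes the clash with the sex strata and means that a second partner's arm is not known in advance. It is preferable to dropping late partners from the primary analysis, which would conflict with the intention-to-treat commitment.
- **Reporting.** Give the number of couples per arm and the estimated ICC.

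The cost is two identifiers, one model term or variance option, and a sentence in the randomisation procedure. Intervals become slightly wider if the correlation is positive. The 90% power statement needs correcting separately.
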